**9.2.** **DOCUMENTATION AND NOTIFICATION**

9.2.1. Documentation and notification of adverse events

The patients must be instructed to contact the investigator immediately in the event of any incident that might require attention with appropriate measures.

In addition, during all the intermediate visits and the final visit the investigator should inquire about incidents, in general terms and without mentioning any symptom in particular. The question might take the following form: ‘Has your health worsened since the last time I saw you?’ If the answer is ‘no’ then no further questions are needed. But if the answer is ‘yes’ then the investigator should document the nature, time, severity, seriousness, and duration of the AE, as well as its cause.

For each AE the following data should be recorded:

. Nature of the event.

. When it began (date and time).

. Interval between the administration of the medication and the onset of the AE.

. Concomitant treatment: product (generic name, indication, dose, dosage interval, presentation, how administered, administration guidelines).

. Duration of AE

. Frequency

. Severity

. Seriousness

. Cause

. Measures taken

. Evolution

The severity of the event is to be evaluated in the following manner:

1. Mild: the patient notes the event or symptom, but tolerates it easily and it does not interfere with daily activities.
2. Moderate: the event or symptom interferes with daily activities.
3. Severe: the event or symptom prevents normal daily activities.

The relationship between an AE and the study medication is to be categorized in accordance with the WHO classification below (all the points need to be reasonably well met):

. Certain:

A clinical event, including a laboratory finding anomaly, the appearance of which is plausibly related to the administration of the medication and which may not be explained by the presence of a concurrent disease or the use of other drugs or chemical substances. The response to withdrawal of the medication (elimination of exposure) should include clinically plausible results. The event must be pharmacologically or phenomenologically definitive, to which end a satisfactory re-exposure procedure should be used, if necessary.

. Probable / presumable

A clinical event, including a laboratory finding anomaly, the appearance of which is sequentially related to the administration of the medication, and which is unlikely to be attributable to a concurrent disease or the use of other drugs or chemical substances and which presents a reasonable clinical response upon withdrawal of the medication (elimination of exposure). No information regarding re-exposure to the medication is needed to fulfill this definition.

. Possible

A clinical event, including a laboratory finding anomaly, the appearance of which is sequentially related to the administration of the medication, but which may also be explained by the presence of a concurrent disease or the use of other drugs or chemical substances. Information regarding the withdrawal of the medication may be non-existent or unclear.

. Improbable

A clinical event, including a laboratory finding anomaly, the temporal relation of which to the administration of the medication renders it unlikely that there is a causal relationship, and for which the use of other drugs or chemical substances or the existence of an underlying disease provide plausible explanations.

. Conditional / non-classified

A clinical event, including a laboratory finding anomaly, reported as an adverse reaction, for which appropriate evaluation requires additional data or for which the data are in the process of being analyzed.

. Non-evaluable / non-classifiable

A report in which an adverse reaction is recorded that cannot be evaluated because the information is insufficient or contradictory, and is not susceptible to being complemented or verified.

. Unrelated

There is enough available information to demonstrate that the etiology is unrelated to the medication in the study.

The measures adopted at the outset of adverse events are to be classified and described in the following manner:

1) None. That is, no changes were made in the study medication.

2) The medication was withdrawn from the study.

3) The adverse event or symptom was treated differently or medically.

4) Other measures (clear explanation).

The course run by the adverse event and its evolution are to be described in the following manner:

1) Recovered / resolved

2) Recovering / under resolution

3) Unrecovered / unresolved

4) Recovered / resolved with sequela(e)

5) Fatal

6) Unknown

Any patient suffering an AE is to receive follow-up after the conclusion of the study until the AE is resolved, or for a maximum of 4 weeks from the end of the patient’s participation in the study. Following the 4-week period, the investigator will issue a declaration concerning the evolution of the AE.

9.2.2. Documentation and notification of serious adverse events

At the moment when participants are included in the study they are to be instructed to contact the investigator in the event of a serious or unexpected AE, so that appropriate measures may be taken.

All SAEs (including death, independently of the cause thereof) occurring during the study or up to 14 days after its conclusion must be reported without delay—that is, within 24 hours—by fax to the study director, regardless of his or her involvement with the administration of the study medication. The minimum information required is the following: name of investigator/study center, patient’s name, patient’s initials, date of the initial dose, date of the last dose, date of the event, description of the event, evaluation of the causality, and the measures taken to counter the event.

Investigators will be provided with a specific form for reporting SAEs. In the event of an SAE, the physician must complete this form as an initial report and then submit it by fax to the project director. If necessary, a follow-up form must also be completed with any new information concerning the SAE; this updated SAE form is also to be submitted to the project director.

The report must contain a detailed description of the observed symptoms and the concomitant treatment given. In addition, the investigator must note whether there is a possible causal relation between the SAE and the medication used in the trial. He or she must carry out follow-up on each SAE until it is resolved or explained satisfactorily. The general procedure for observation must be applied to the fullest, with collection and analysis of the pharmacological risks (in matters of regulation) under the terms of the National Law on Medicines.

The sponsor may only unmask the treatment of isolated cases if it is a question of the safety of the study participant. When an intolerable SAE occurs, the patient will be withdrawn from the clinical trial, when the investigators deems this to be in order, and symptomatic treatment will then be administered. The measures taken are to be duly recorded in the CRF.

**10. ETHICAL CONSIDERATIONS**

This study will be carried out under the terms of the Helsinki Declaration (in its latest applicable version), international standards, and the applicable national regulations (see Section 10.3).

**10.1. INFORMATION FOR THE PATIENT AND PATIENT CONSENT**

Before their inclusion in this clinical trial, patients will be informed that participation is entirely voluntary and that they may withdraw at any time without the need to provide an explanation and without their doing so having any repercussion on their normal medical care.

Patients will be given information concerning the therapy of the study and its possible adverse effects. They will also be told about the aims of the study and its clinical significance. The explanation will also include information regarding insurance protection that they will be afforded and their obligations as insured parties.

The patients will be given ample time and opportunity to resolve any questions that they may have about the study. Furthermore, they will be given an information sheet containing all the essentials concerning the study, in writing. Appendices 7 and 8 represent the patient information sheet and the informed consent sheet.

Patient consent in writing must be obtained before beginning the study. By signing the informed consent, the patient declares that he or she is participating voluntarily in the trial with the intention of following the protocols that govern it and the instructions provided by the investigator, as well as being willing to answers questions posed during the course of the trial. Again, each patient will be reminded that participation in the study is entirely voluntary and that withdrawal from it may be made at any time without the need for any explanation. The investigator will keep a copy of the signed informed consent form of the patient in a location set aside for that purpose.

**10.2. ETHICAL COMMITTEE**

In line with the applicable national guidelines, before the beginning of the study this protocol and the patient informed consent and information sheets will be submitted to the ethical committee, for assessment under its governing criteria.

**10.3. INSURANCE POLICY**

The present study will undertake to investigate the effect of a gluten-free diet in comparison to a diet containing gluten (with the amount found in an average diet). A gluten-free diet is well tolerated, has all the macronutrients and micronutrients needed for proper nutrition, and is not associated with any side effects.

Nevertheless, an insurance policy will need to be taken out to cover civil liability.

**10.4. LEGAL CONSIDERATIONS**

The study must be carried out under the terms of the protocol, observing the Good Clinical Practice guidelines and the applicable regulations.

10.4.1. Helsinki Declaration

The study will be carried out in accordance with the ‘Ethical Principles for Medical Research Involving Human Subjects’ enshrined in the 18th General Assembly of the World Medical Association (WMA) in Helsinki (1964), and of its amendments, adopted by the 29th, 35th, 41st, 48th, and 52nd General Assemblies of the WMA (Tokyo 1975, Venice 1983, Hong Kong 1989, Somerset West 1996, and Edinburgh 2000), as well as the Clarification Note concerning Paragraph 29 added by the General Assembly of the WMA in Washington 2002, and the Clarification Note concerning Paragraph 30 added by the General Assembly of the WMA in Tokyo 2004.

10.4.2. Other legal considerations

The other legal underpinnings of this clinical trial are the following:

• Topic E6 of the ICH, Guides for Good Clinical Practice, including the subsequent erratum on pass 4, September 1997.

• Directive 2001/20/CE (April 4, 2001).

• Directive of the European Commission 2005/28/EC (April 8, 2005).

• National regulatory requirements / guides for countries participating in clinical trials.

The medical expert and all of the researchers will be provided by the investigator with an up-to-date brochure fully detailing the state of both preclinical and clinical knowledge regarding the medication to be used in the study. Whenever new information is available, an updated version of the brochure, or an addendum to it, will be added to investigators’ file.

10.4.3. Approval of regulatory authorities

No patients may be included in the study until all of the requirements of the national health authorities have been met. The trial will commence only following approval by the relevant ethical committee and the agreement of the corresponding national health authority.

**11. ACCOUNTABILITY**

The sponsor, the researchers, and all of the personnel involved in the clinical trial must be in agreement to carry it out under the Good Clinical Practice of the ICH.

In accordance with Spanish legislation (R.D. 223/2004) and the directives of the European Community (91/507/CEE), all clinical trials, and in all their phases, including those examining bioavailability and bioequivalence, are to be carried out in line with the norms of Good Clinical Practice (GCP).

These norms are designed to help insure that clinical investigation is carried out in line with the highest quality standards, following ethical criteria based on the Helsinki Declaration and subsequent development, and with a guaranteed medical team. The GCP guidelines cover the design, management, performance, compliance, monitoring, auditing, recording of data, analysis, and handling of information in clinical trials to insure that the data and results obtained are correct and credible, and to protect the rights, integrity, and confidentiality of trial subjects.

The ICH (International Conference on Harmonisation of Technical Requirements for Registration of Pharmaceuticals for Human Use) Good Clinical Practice principles are as follows:

1. Clinical trials should be conducted in accordance with the ethical principles that have

their origin in the Declaration of Helsinki, and that are consistent with GCP and the

applicable regulatory requirement(s).

2. Before a trial is initiated, foreseeable risks and inconveniences should be weighed against

the anticipated benefit for the individual trial subject and society. A trial should be

initiated and continued only if the anticipated benefits justify the risks.

3. The rights, safety, and well-being of the trial subjects are the most important

considerations and should prevail over interests of science and society.

4. The available nonclinical and clinical information on an investigational product should be

adequate to support the proposed clinical trial.

5. Clinical trials should be scientifically sound, and described in a clear, detailed protocol.

6. A trial should be conducted in compliance with the protocol that has received prior

institutional review board (IRB)/independent ethics committee (IEC) approval/favorable

opinion.

7. The medical care given to, and medical decisions made on behalf of, subjects should

always be the responsibility of a qualified physician or, when appropriate, of a qualified

dentist.

8. Each individual involved in conducting a trial should be qualified by education, training,

and experience to perform his or her respective task(s).

9. Freely given informed consent should be obtained from every subject prior to clinical trial

participation.

10. All clinical trial information should be recorded, handled, and stored in a way that allows

its accurate reporting, interpretation and verification.

11. The confidentiality of records that could identify subjects should be protected, respecting

the privacy and confidentiality rules in accordance with the applicable regulatory

requirement(s).

12. Investigational products should be manufactured, handled, and stored in accordance with

applicable good manufacturing practice (GMP). They should be used in accordance with

the approved protocol.

**11.1. Direct access to the source documents in accordance with the ICH GCP guidelines**

In accordance with the ICH GCP guidelines, researchers and research centers must provide direct access to source data and documents to allow for activity related to trial monitoring, auditing, independent ethical committee (IEC) review, and legally mandated inspection. All participants have consented (by signing their written informed consent) to direct access to their original medical records for trial-related monitoring, IEC review, and inspection. The contents of the protocol must include identification of all the data to be recorded directly in the CRF (that is, without prior written or electronic recording) which are to be considered source information.

The patient file must include the following information as a minimum:

• Patient demographic information (name, address, date of birth, sex).

• Height and weight (baseline).

• Underlying study illness, date of initial symptoms, and date of first diagnosis of study illness.

• Results of prior endoscopic and histological examinations, if appropriate.

• Medications taken for the illness in question.

• Concomitant illnesses and medications taken for them.

• Proof that the patient is taking part in the study.

• Date of each visit.

• Results of explorations carried out during this trial.

• Activity of the study illness / general state of the patient at each visit.

• All laboratory findings generated in this study.

• Adverse events and adverse drug reactions.

• Reasons for withdrawal, if appropriate.

All other variables may be entered directly into the CRF and will be considered source data.

**11.2. Filing of essential documents**

11.2.1. Investigator

The investigator must keep his or her copies of the CRFs, the signed informed consent forms, the identification list of patients, and the patient records with the original data, for a minimum period of 15 years.

11.2.2. Sponsor

The sponsor will keep all the CRFs and all additional documentation related to the trial for a minimum period of 15 years.

**12. ADDITIONAL FACTORS**

**12.1. PROCEDURES FOR AMENDING THE PROTOCOL**

Any modification of the present protocol that does not involve a substantial change may be made by common consensus, in writing, between the principal investigator and the sponsor.

In the event that the modification(s) involve substantial changes in the original protocol, they must be submitted to the IEC for consideration.

**12.3. TRIAL CANCELLATION**

In the event of cancellation of the trial, the IEC of the hospital must be informed of the reasons for the cancellation.

**13. STATISTICAL ANALYSIS**

The calculation for the sample size is based on the main variable of efficacy—that is, the rate of recidivism at 6 months. On the basis of results of previous studies it was determined that the rate of recidivism with the reintroduction of gluten would be 80%, and with placebo 20%. Assuming a 10% patient drop-out rate, an alpha value of 5%, and statistical power (beta) of 80%, for a bilateral test it was calculated that 10 patients would be needed for each patient group (bearing in mind that analyzing the results would require a Chi-square test with Yates correction). The total number, then, is 20 patients.

Excluded from this analysis are those subjects presenting significant departures from the protocol.

All of the evaluations of the primary and secondary variables, both of efficacy and of safety, are understood in the exploratory sense (alpha=0.05, bilateral).

The Chi-square test with Yates correction will be used for independent groups and the Fisher exact test for qualitative variables. For intergroup comparison of the quantitative variables, the Student-t test will be used for parametric variables, and the Mann-Whitney U-test for non-parametric variables.

The finding of values for differences of p less than 0.05 will be considered significant. The rates for clinical remission between treatment groups will be expressed proportionally with the corresponding bilateral interval of confidence of 95%, as an estimation of therapeutic effect.

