# 1. SUMMARY OF THE STUDY

| **Title** | Lymphocytic enteritis with negative coeliac serology and clinical and histological response to a gluten-free diet: double-blind randomized clinical trial with rechallenge of gluten vs. placebo. | |
| --- | --- | --- |
| **Study code** | EL-DSG/07/2011 | |
| **Objectives** | To demonstrate hypersensitivity to gluten in patients with lymphocytic enteritis, and clinical response and histology of a gluten-free diet despite the presence of IgA negative tissue anti-transglutaminase antibodies. | |
| **Treatment** | Sachets with gluten (10 g) or placebo (maltodextrin: 10 g): 1 sachet every 12 hours. | |
| **Study design** | Prospective, randomized, double-blind, placebo-controlled, with parallel groups of gluten rechallenge vs. placebo, for 24 weeks, in patients following a gluten-free diet.   - Group A: Powdered gluten (10 g every 12 hours) - Group B: Placebo (10 g every 12 hours)   Determination of digestive clinical state, adherence to diet, coeliac serology, histology, flow cytometry, and tissue anti-transglutaminase antibodies in intestinal mucus membrane, at baseline and after gluten rechallenge or placebo (whether clinical digestive symptoms reappear at 4 or 12 weeks, or at the conclusion of the study at 24 weeks). | |
| **Study population** | Inclusion criteria:  1. Signed informed consent  2. Age 18 or older  3. Confirmed histological diagnosis of lymphocytic enteropathy (LE)  5. Coeliac-positive genetic study (HLA-DQ2 and/or HLA-DQ8)  6. Negative coeliac serology  7. Complete clinical and histological response to gluten-free diet  8. Initial clinical signs with or without extra-intestinal manifestations | |
|  | Exclusion criteria:  1. Inability to adhere to the scheduled visits or other protocol requirements, in the judgement of the investigator  2. Participation in a clinical trial in the previous 30 days, simultaneous participation in a trial, or prior participation in the present study  3. History of gluten-sensitive enteropathy with villous atrophy or positive serology  4. Lymphocytic enteropathy or initial response to gluten-free diet but following a normal diet at the time of selection | |
| **Sample size** | 20 patients | |
| **Length of treatment** | 24 weeks | |
| **Primary efficacy variables** | Reappearance of clinical digestive signs and histological recurrence | |

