**8. DEVELOPMENT OF TRIAL AND ASSESSMENT OF RESPONSE**

**8.1. PRINCIPAL AND SECONDARY ASSESSMENT VARIABLES**

**Efficacy criteria**

- Primary efficacy evaluation variable: Reappearance of clinical digestive signs (24 weeks)
- In addition, secondary efficacy variables will be evaluated:
  - Clinical signs at 4 weeks
  - Clinical signs at 12 weeks
  - Flow cytometry to measure percentage of lymphocytes CD3+ gamma-delta+ and CD3- in intestinal mucus membrane
  - Assessment of IgA tissue anti-transglutaminase antibodies in the intestinal mucus membrane
  - IgA tissue anti-transglutaminase antibodies in serum and anti-endomysium antibodies
  - Quality of life according to the GIQLI questionnaire.
  - Histological changes on biopsy in the distal duodenum

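### Yates chi-square or Fisher, as fixed for the primary relapse comparison, gives 63.5% power at 10 per arm, not the stated 80%; a less conservative exact test on the same outcome gives 80.5%

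*Protocol*

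**What the plan says.** Section 8.1 makes the return of digestive signs at 24 weeks the primary efficacy variable. Section 13 sizes the trial on it: "The calculation for the sample size is based on the main variable of efficacy—that is, the rate of recidivism at 6 months". The inputs there are relapse of 80% with gluten and 20% with placebo, alpha 5%, power 80% and 10% drop-out. From these, "for a bilateral test it was calculated that 10 patients would be needed for each patient group", with the remark that "analyzing the results would require a Chi-square test with Yates correction". For the analysis, "The Chi-square test with Yates correction will be used for independent groups and the Fisher exact test for qualitative variables". It is not clear from that sentence which of the two governs the primary comparison; the sample-size remark points to Yates.

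Relapse is also observed in time. The Section 1 summary ties the closing work-up to "whether clinical digestive symptoms reappear at 4 or 12 weeks, or at the conclusion of the study at 24 weeks", and Section 8.1 lists clinical signs at 4 and 12 weeks as secondary variables. Section 13 names no test that uses the timing of relapse.

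**The concern.** With 20 patients, the choice of test for a 2x2 table matters a good deal. Yates' correction and Fisher's test keep the error rate far below the nominal 5% in arms of 10, and the cost is power. If Section 13 is followed as written, a true difference as large as 80% against 20% would be missed in more than one trial in three, although the section says one in five. The protocol fixes this itself: the test is written into the sample-size rationale, not left open for a later analysis plan.

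**Working it through.** **Inputs.** From Section 13: relapse 0.80 and 0.20, two-sided alpha 0.05, target power 0.80, drop-out 10%, 10 per arm. From Section 5.1: 1:1 allocation.

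**1. The plan's own figure.** The usual pooled formula gives n = [1.960·√(2·0.5·0.5) + 0.842·√(0.8·0.2 + 0.2·0.8)]² / 0.6² = (1.386 + 0.476)² / 0.36 = 9.63, so 10 per arm. This matches the protocol, but it has no continuity correction and no drop-out. With the correction, n = (9.63/4)·[1 + √(1 + 4/(9.63·0.6))]² = 12.75, so 13 per arm. Allowing for drop-out, 13/0.9 = 14.4, so 15 per arm. Ten per arm therefore does not follow from the full set of stated inputs.

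**2. Exact power of the named tests.** Power is the sum of Bin(a; 10, 0.8)·Bin(b; 10, 0.2) over all tables (a relapses on gluten, b on placebo) with p < 0.05. At 10 per arm, Yates and Fisher reject the same tables. With gluten higher these are 5 or more v 0, 7 or more v 1, 8 or more v 2, 9 or more v 3, and 10 v 4 or 5. Together they carry **63.5%** probability.

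A result of 7 v 2 shows what is lost:
- Yates: 20·(|7·8 − 3·2| − 10)² / (10·10·9·11) = 20·40²/9900 = 3.23, below the critical value 3.84.
- Uncorrected: 20·50²/9900 = 5.05, above it.

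With equal relapse rates in both arms, Yates and Fisher reject 0.76% of the time at a common rate of 20% or 80%, and 1.28% at 50%, which is their maximum.

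**3. Same outcome, less conservative exact test.** At 10 per arm, Boschloo's two-sided test also rejects 4 v 0, 6 v 1, 7 v 2, 8 v 3, 9 v 4 and 10 v 6 (and their mirror images). At the planned rates these add 0.0006 + 0.0236 + 0.0608 + 0.0608 + 0.0236 + 0.0006 = 0.170, and 0.635 + 0.170 = **0.805**. Its maximum size is 4.2%.

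**4. After drop-out.** The table gives exact power; the 9-per-arm row takes one loss in each arm.

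| Evaluable per arm | Yates | Fisher | Uncorrected chi-square | Boschloo |
|---|---|---|---|---|
| 10 | 63.5% | 63.5% | 80.5% | 80.5% |
| 9 | 51.9% | 62.5% | 76.1% | 72.1% |

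The uncorrected test is not guaranteed to hold its level: at 9 per arm its size is already 5.01% at a common rate of 50%. When 10% drop-out falls at random over arms and visits (simulated, error about 0.9 points), Yates has 60–62% with drop-outs excluded and 55–57% with drop-outs counted as non-relapse. The 52% is thus specific to one loss per arm.

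**5. What relapse timing adds.** This is the simulated power of an exact permutation log-rank test on week 4, 12, 24 or none, at 10 per arm with complete data. All timing patterns are assumptions; splits are shares of relapses at weeks 4/12/24.

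| Timing | Power |
|---|---|
| Constant hazards | 78–79% |
| Even thirds, both arms | 74% |
| 50/30/20, both arms | 73% |
| 90/10/0, both arms | 68% |
| All relapses at one visit | 63.5% (same as Fisher) |
| Gluten 60/30/10, placebo 10/30/60 | 88% |
| Gluten 20/30/50, placebo 50/30/20 | 66% |
| Gluten 10/30/60, placebo 60/30/10 | 62% |
| Gluten 10/20/70, placebo 80/15/5 | 59–60% |

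Like for like, the asymptotic log-rank test differs from the uncorrected chi-square by only about −1 to +2 points when both arms share a timing pattern or hazards are constant. Most of the gain over Yates and Fisher therefore comes from leaving a very conservative test, not from using time.

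**The case against.** A fixed 24-week yes/no endpoint is a legitimate choice, Yates and Fisher are valid tests, and Section 13 calls all its evaluations exploratory. All of that stands: the tests do not inflate the error rate, and the endpoint needs no defence. It does not rescue the power statement, because the same section sets 80% power, a 5% two-sided level and significance at p below 0.05, and the named tests fall short of that power at the chosen size.

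A reader might go further and infer that collapsing relapse to yes/no throws away timing and costs 10 to 15 points of power, so that a log-rank test should become primary. The documents do not support this. The yes/no outcome reaches 80.5% once the test is changed, at least as much as the log-rank test under shared timing or constant hazards. The log-rank advantage depends on a relapse pattern the protocol does not give, and in adverse patterns it falls below Yates. Timing is also not lost to the trial, since weeks 4 and 12 remain secondary variables.

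A reader might also infer that patients lost after a symptom-free visit are bound to be mishandled. That is too strong. Section 8.4 requires early withdrawals to be seen within 7 days of the last administration, and Section 8.3 plans assessments at withdrawal. Because Section 8.4 lists disease progression and intolerable adverse events among withdrawal reasons, censoring could itself be informative. Detailed missing-data rules may properly sit in an analysis plan that is not shown.

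**Conclusion.** The point holds as one about the choice of test. With complete data and the protocol's own rates, Yates and Fisher give 63.5% power at 10 per arm, 16.5 points below the stated 80%. One loss per arm leaves Yates at 51.9% and Fisher at 62.5%. These figures are exact and rest only on the stated 80% and 20% and on independent patients. Changing the test recovers 17.0 points at 10 per arm (80.5 − 63.5) and, at 9 per arm, 20.2 over Yates (72.1 − 51.9) or 9.6 over Fisher (72.1 − 62.5). It does not restore 80% after drop-out. The case for a timing-based test is weaker and conditional: it can use partial follow-up, but its power is an assumption-driven range. This is a correctable weakness in Section 13, not an invalid analysis.

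**What to change.** In Section 13, replace Yates/Fisher for the primary comparison with one named, less conservative exact test on the same 24-week yes/no outcome, such as Boschloo's two-sided unconditional test. Keep the 24-week relapse proportions and their 95% interval as the effect estimate. Restate the power for that test: 80.5% with 10 evaluable per arm and 72.1% with 9. If 80% after drop-out is required, the sample size must also rise.

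Add an exact permutation log-rank test on the visit of first relapse (weeks 4, 12 and 24) as a supportive analysis. It should use the exit visit and the partial follow-up of drop-outs, and state the assumption made in censoring.

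The change of test is wording in Section 13, with no extra visits, patients or procedures. If it is judged substantial, Section 12.1 sends it to the ethics committee. The downsides are small: the unconditional test is less familiar and needs software support, and the log-rank result is less directly tied to the 24-week difference.

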**6.3. EXPECTED NUMBER OF SUBJECTS**

The estimated sample size is 20 patients (10 for each treatment group) who will be evaluated on the basis of intention to treat.

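### Ten patients per group do not give the stated 80% power with the Yates test and 10% drop-out: exact power is about 64%, or about 52% with 9 evaluable per group

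*Protocol*

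**What the plan says.** Section 13 of the protocol bases the sample size on the relapse rate at 6 months. It expects 80% relapse on gluten and 20% on placebo. It continues with "Assuming a 10% patient drop-out rate", a 5% alpha and 80% power (labelled beta, an obvious slip that changes nothing), and concludes that "for a bilateral test it was calculated that 10 patients would be needed for each patient group". A bracket adds the test the calculation is meant to serve: "bearing in mind that analyzing the results would require a Chi-square test with Yates correction". The total is given as 20.

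Section 6.3 repeats 20 patients, 10 per group, and says they will be evaluated by intention to treat. Section 13 says that subjects with significant departures from the protocol are excluded from the analysis. It also names Fisher's exact test for qualitative variables and describes all evaluations as exploratory at a two-sided alpha of 0.05.

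**The concern.** The sentence gives every input needed to repeat the calculation and says that two allowances, for the Yates correction and for drop-out, are already in the answer. Both raise the required number. Yet 10 per group is what the standard formula gives with neither.

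If so, the 80% power is a property the design does not have. Anyone judging whether the trial can meet its objective of demonstrating gluten hypersensitivity would be relying on a wrong figure. A non-significant result could then be given more weight as evidence against gluten sensitivity than a trial of this size can bear.

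**Working it through.** **Inputs.** From section 13: relapse rates p1 = 0.80 and p2 = 0.20 (difference d = 0.60), two-sided alpha 0.05 (z = 1.96), power 80% (z = 0.8416), drop-out 10%, Yates-corrected chi-square. From section 5.1: 1:1 allocation. The mean rate is 0.50, and p1(1−p1) + p2(1−p2) = 0.16 + 0.16 = 0.32.

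**Step 1: reproduce the plan's figure.** The pooled formula without correction is

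n = [1.96·√(2·0.5·0.5) + 0.8416·√0.32]² / 0.60² = (1.386 + 0.476)² / 0.36 = 9.63, rounded up to 10.

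This matches the protocol, but it contains neither the Yates correction nor drop-out.

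**Step 2: add the Yates correction.**

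n' = (9.63/4)·[1 + √(1 + 4/(9.63·0.60))]² = 12.75, rounded up to 13 evaluable per group.

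**Step 3: add drop-out.** 13/0.90 = 14.4, rounded up to 15 per group, 30 in total.

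**Step 4: try a more lenient formula.** With unpooled variance, n = (1.96 + 0.8416)²·0.32/0.36 = 6.98. With the correction this becomes 10.03, so 11 per group before drop-out. Afterwards it is 12 (10.03/0.90 = 11.1) or 13 (11/0.90 = 12.2). This does not give 10 either.

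**Step 5: exact power.** For each pair of group sizes, every possible 2x2 table was listed and the test applied at p < 0.05. The binomial probabilities of the rejecting tables were summed at 80% versus 20%.

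| Evaluable per group | Yates | Fisher | Uncorrected chi-square |
|---|---|---|---|
| 9 / 9 | 51.9% | 62.5% | 76.1% |
| 10 / 10 | 63.5% | 63.5% | 80.5% |
| 11 / 11 | 73.4% | 73.4% | 86.7% |
| 12 / 12 | 81.2% | 81.2% | 91.1% |

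At 10 per group, 80% appears only in the uncorrected column, and section 13 does not plan that test.

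**Step 6: drop-out as a random event.** If each patient independently has a 10% chance of being lost, average power from 10 enrolled per group is 59.0% with Yates and 64.6% with Fisher.

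**Step 7: size that meets the stated inputs.** By exact Yates power, 12 evaluable per group is the smallest size that reaches 80%. Then 12/0.90 = 13.3, so 14 enrolled per group (28 in total). The corrected formula gives 15 per group (30 in total).

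**Step 8: effect needed for 80% power.** With Yates and 20% relapse on placebo, the gluten relapse rate would have to be about 88% at 10 per group, or about 93% at 9 per group.

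**Illustration.** With 9 evaluable per group, a result of 7/9 versus 2/9, close to the planned effect, has a Yates p-value of 0.059.

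**The case against.** The strongest points on the other side are these.

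- **The 52% is a low point.** Power of a discrete test does not rise smoothly with size. With Yates, 10 versus 9 gives 67.3%, more than 10 versus 10. This stands: the 52% belongs to exactly 9 versus 9 with Yates, and 59% is the fairer summary of 10% drop-out. Neither is near 80%.
- **The test is ambiguous.** Section 13 also assigns Fisher's test to qualitative variables, and relapse is one. Under Fisher, drop-out costs almost nothing. This also stands, but Fisher still gives only 62.5% to 64.6%.
- **Intention to treat keeps all 20 patients.** Section 6.3 says so, although section 13 excludes significant protocol departures. Complete data on 20 patients still give 63.5%. If drop-outs stay in and are all counted as non-relapse (72% versus 18%) or all as relapse (82% versus 28%), an assumption because the protocol is silent, Yates power is about 51%.
- **The origin of the 10 is inferred.** The protocol names no formula or software. A one-sided, unpooled, corrected calculation with drop-out also gives 10, but it contradicts the stated two-sided test. Omission of both allowances is the probable cause, not a proven one. The error does not depend on it.
- **The evaluations are exploratory.** That softens the consequence, and the type I error, estimate and confidence interval are unaffected. It does not make a stated power correct.

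**Conclusion.** The sample-size statement is wrong as written. At the protocol's own rates, 10 per group gives 63.5% power with either named test, about 16 points short of the claim. Allowing for 10% drop-out, power averages 59.0% with Yates and 64.6% with Fisher; at exactly 9 per group it is 51.9% and 62.5%. The trial would miss significance in more than a third of repetitions, and in nearly half with Yates at 9 per group.

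These figures assume that the true rates are 80% and 20%, that patients are independent and, for the 59.0% and 64.6%, that losses are random and unrelated to outcome. No choice of Yates or Fisher, and no reading of the analysis set examined here, brings 20 patients to 80%.

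**What to change.** Keep 20 patients and correct the paragraph in section 13. Suggested wording: *With 10 patients per group and the Yates-corrected chi-square test, exact power to detect 80% versus 20% relapse at a two-sided 5% level is about 64%. With 10% random drop-out it averages about 59%, and it is about 52% if exactly 9 per group are evaluable.*

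Delete the claim that 10 per group already allows for the Yates correction and drop-out. In the same edit, name one test for the primary comparison. If that is Fisher's, the three figures become about 64%, 65% and 63%.

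The cost is one rewritten paragraph and a less favourable stated power, with no extra patients or procedures. The correction makes the statement true but does not raise the power. If the sponsor wants 80%, the alternative is to enrol 14 per group (28 in total, by exact power) or 15 per group (30 in total, by formula), that is, 8 to 10 more patients.
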